### Sample size

The six-arm design allows evaluation of:

The effect of the novel treatment regimens (3HP and 1HP) vs standard-of-care regimen (3HR), under routine treatment support.The effect of additional treatment support vs routine treatment support for each individual regimen.

A total of 920 participants are to be recruited. This provides 80% power for each of the following comparisons:

Arm 3 vs Arm 1—that is, 3HP+routine treatment support vs 3HR+routine treatment support.Arm 5 vs Arm 1—that is, 1HP+routine treatment support vs 3 HR+routine treatment support.Arm 2 vs Arm 1—that is, 3HR+additional treatment support vs 3HR+routine treatment support.Arm 4 vs Arm 3—that is, 3HP+additional treatment support vs 3HP+routine treatment support.Arm 6 vs Arm 5—that is, 1HP+additional treatment support vs 1HP+routine treatment support.

The power calculations assume the following:

70% adherence rate in Arm 1.3HP and 1HP improve adherence rate by 15% (absolute difference) compared with 3HR, respectively, with routine treatment support.^18 23 24^Compared with routine treatment support, additional treatment support improves adherence rate by 15% for 3HR, and 10% for 3HP and 1HP, respectively.^12^Two-sided alpha 5% (see below for type I error considerations).Average number of participants enrolled per household is 2, taking into account the average household size in UK.^25^Intra-class correlation within a household is 0.1

The 70% adherence rate assumed for Arm 1 is based on the 77% LTBI treatment completion rate reported from the Public Health England LTBI testing and treatment database for 2018.^26^

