**Methods and analysis:**

A pragmatic multicentre, open-label, randomised controlled trial assessing the effect of novel short-course rifapentine-based regimens for TB prevention and additional theory-based treatment support on treatment adherence against standard-of-care. Participants aged between 16 and 65 who are eligible to start TB preventive therapy will be recruited in England. 920 participants will be randomised to one of six arms with allocation ratio of 5:5:6:6:6:6: daily isoniazid +rifampicin for 3 months (3HR), routine treatment support (control); 3HR, additional treatment support; weekly isoniazid +rifapentine for 3 months (3HP), routine treatment support; weekly 3HP, additional treatment support; daily isoniazid +rifapentine for 1 month (1HP), routine treatment support; daily 1HP, additional treatment support. Additional treatment support comprises reminders using an electronic pillbox, a short animation, and leaflets based on the perceptions and practicalities approach. The primary outcome is adequate treatment adherence, defined as taking ≥90% of allocated doses within the pre-specified treatment period, measured by electronic pillboxes. Secondary outcomes include safety and TB incidence within 12 months. We will conduct process evaluation of the trial interventions and assess intervention acceptability and fidelity and mechanisms for effect and estimate the cost-effectiveness of novel regimens. The protocol was developed with patient and public involvement, which will continue throughout the trial.

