### Statistical methods

The estimands for the primary analyses are defined in table 2. The primary analyses will compare the proportion of participants with adequate adherence between arms using the following approach: (a) Arm 3 vs Arm 1—that is, 3HP+routine treatment support vs 3HR+routine treatment support; (b) Arm 5 vs Arm 1—that is, 1HP+routine treatment support vs 3HR+routine treatment support and (c) Arm 2 vs Arm 1—that is, 3HR+additional treatment support vs 3HR+routine treatment support

**Table 2 T2:** Definition of the estimands for the primary analyses

Attribute	Definition
Treatments	The primary analyses are based on the following comparisons: (a) Arm 3 vs Arm 1—that is, 3HP+routine treatment support vs 3HR+routine treatment support (b) Arm 5 vs Arm 1—that is, 1HP+routine treatment support vs 3HR+routine treatment support (c) Arm 2 vs Arm 1—that is, 3HR+additional treatment support vs 3HR+routine treatment support If comparison (a) shows 3HP improves adherence compared with 3HR, then additional treatment support will be formally tested for 3HP by comparing Arm 4 vs Arm 3—that is, 3HP+additional treatment support vs 3HP+routine treatment support. Additional treatment support will be similarly assessed for 1HP.
Population	Adults aged 16–65 years diagnosed with LTBI and eligible for LTBI treatment.
Endpoint	Adequate treatment adherence, defined as taking ≥90% of allocated doses within the allowable time frame.
Intercurrent events	The main intercurrent events and how they will be handled in the estimand are as follows: Failure to collect all prescriptions—composite and treatment policy strategies lead to same estimated effect. Early treatment discontinuation for any reason including adverse event(s) and active TB: a treatment policy strategy will be used, that is, the participant is considered to have stopped treatment regardless of the occurrence of the intercurrent event.
Population-level summary measure	Risk ratio for adequate treatment adherence comparing the relevant arms.

LTBI, latent tuberculosis infection.

If comparison (a) shows 3HP improves adherence compared with 3HR, then additional treatment support will be formally tested for 3HP by comparing Arm 4 vs Arm 3—that is, 3HP+additional treatment support vs 3HP+routine treatment support; otherwise, the adherence rates will be compared between these arms as exploratory analyses. Additional treatment support will be similarly assessed for 1HP.

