All randomised patients will be included in the primary analyses, apart from those subsequently found to have had TB disease at baseline but enrolled in error (modified intention-to-treat approach). The risk ratio (with 95% CI) for adequate treatment adherence comparing the relevant arms will be estimated using log-binomial generalised linear mixed models, allowing for intra-household correlation.

Type I error adjustment for multiple comparisons is not deemed necessary since:

The research hypotheses corresponding to comparisons (a), (b) and (c) are considered sufficiently distinct.^27–29^The effect of additional treatment support vs routine support is being evaluated in non-overlapping populations for 3HR, 3HP and 1HP, respectively.The closed test approach whereby the effect of additional treatment support will only be formally tested for 3HP if there is evidence that 3HP improves adherence compared with 3HR with routine treatment support protects the type I error. This approach will also be used for the assessment of additional treatment support for 1HP.

For participants who have collected all prescriptions but are lost to follow-up before completing treatment, the adherence data until the end of allocated period can still be downloaded remotely from the Wisepill monitor box to ascertain whether adequate treatment adherence is achieved; these data will be included in the primary analyses. In sensitivity analyses, the primary outcome will be imputed for these patients using multiple imputation by chained equations, with imputation to be conducted separately by study arm. Sensitivity analyses will also be performed assuming no drug intake from the last follow-up visit attended.

Supplementary analyses will consider different definitions of adequate treatment by varying the minimum proportion of doses required to have been taken, and different allowable time frames for making up missed doses. In addition, other analysis populations will be considered, including intention-to-treat and per protocol (including only participants who commenced their original allocated trial intervention). Planned exploratory subgroup analyses, will examine outcomes in predefined subgroups.

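### The stated 80% power for Arm 4 vs Arm 3 and Arm 6 vs Arm 5 leaves out the plan's own precondition for testing them; the chance of a formal positive result is about 67-69%

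*Protocol article*

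**What the plan says.** The Sample size section gives one total and one power figure: "A total of 920 participants are to be recruited. This provides 80% power for each of the following comparisons". The list that follows puts five comparisons on an equal footing: Arm 3 vs 1, Arm 5 vs 1, Arm 2 vs 1, Arm 4 vs 3 and Arm 6 vs 5. The assumptions beneath it cover adherence rates, two-sided alpha of 5%, household size and intra-household correlation. None concerns the order of testing, although the alpha entry refers the reader forward to the type I error discussion.

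Statistical methods (text and Table 2) then sets an order: "If comparison (a) shows 3HP improves adherence compared with 3HR, then additional treatment support will be formally tested for 3HP". If that condition is not met, the two 3HP arms are compared only on an exploratory basis. The type I error paragraph repeats that the support effect "will only be formally tested for 3HP if there is evidence that 3HP improves adherence compared with 3HR" with routine support, and applies the same approach to 1HP. There the condition serves as one of three reasons for making no multiplicity adjustment. Its effect on power is not mentioned.

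**The concern.** A comparison that is formally tested only after another has succeeded can give a formal positive result only if both steps succeed. The probability of that is lower than the power of the second test alone. Arm 3 also has opposite roles in the two steps: it is the experimental arm against Arm 1 and the comparator for Arm 4. A high observed rate in Arm 3 helps the first step and works against the second, so the two test statistics are negatively correlated. Arm 5 plays the same double role for 1HP.

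What is at stake is how the design is described. The support effect is part of the primary objective, and the strengths and limitations list says the trial is powered to evaluate it. A funder or reader would take 80% as the chance that the trial formally demonstrates the assumed benefit of support within 3HP and within 1HP, and under the stated rule it is not.

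**Working it through.** **Inputs (Sample size section and Abstract).** Total 920; allocation 5:5:6:6:6:6 (sum 34); adherence 70% in Arm 1, 85% in Arms 2, 3 and 5, and 95% in Arms 4 and 6 ("additional treatment support improves adherence rate by 15% for 3HR, and 10% for 3HP and 1HP, respectively"); two-sided alpha 5%; two participants per household; intra-household correlation 0.1. No loss is applied, because all randomised participants enter the analysis apart from those found to have had TB disease at baseline.

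**Arm sizes.** 920 × 5/34 = 135.3 in Arms 1-2; 920 × 6/34 = 162.4 in Arms 3-6. Design effect 1 + (2 − 1) × 0.1 = 1.1. Effective sizes are 135.3/1.1 = 123.0 and 162.4/1.1 = 147.6.

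**Step 1: reproduce the plan's figure.** Power = Φ[(|difference| − 1.96 × SE0)/SE1], where SE0 uses the pooled proportion, SE1 uses the separate proportions, and there is no continuity correction.
- Arm 3 vs 1 and Arm 5 vs 1 (70% vs 85%): SE0 = 0.05042, SE1 = 0.05071; (0.15 − 0.0988)/0.05071 = 1.009; power 84.4%.
- Arm 2 vs 1 (70% vs 85%): SE0 = 0.05325, SE1 = 0.05238; (0.15 − 0.1044)/0.05238 = 0.871; power 80.8%.
- Arm 4 vs 3 and Arm 6 vs 5 (85% vs 95%): SE0 = 0.03492, SE1 = 0.03443; (0.10 − 0.0684)/0.03443 = 0.916; power 82.0%.

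In reverse, 80% power needs 121 × 1.1 = 133.1 per arm for Arm 2 vs 1, a total of 133.1 × 34/5 = 905. It needs 141 × 1.1 = 155.1 per arm for Arm 4 vs 3, a total of 155.1 × 34/6 = 879. Both lie within 920. The stated 80% is therefore the power of each comparison on its own, and it reproduces.

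**Step 2: add the precondition.** Assume the first step succeeds when Arm 3 vs 1 is significant at two-sided 5% in favour of 3HP.
- Variances of the observed proportions: Arm 1, 0.70 × 0.30/123.0 = 0.001707; Arm 3, 0.85 × 0.15/147.6 = 0.000864; Arm 4, 0.95 × 0.05/147.6 = 0.000322.
- Correlation of the two contrasts: −0.000864/√[(0.001707 + 0.000864) × (0.000864 + 0.000322)] = −0.495.
- Probability that both steps succeed, from the bivariate normal at 1.009 and 0.916 with that correlation: 66.9%. Ignoring the correlation, 0.844 × 0.820 = 69.2%.
- A simulation of 400,000 trials with household pairs (correlation 0.1) gives 69.4% with a pooled z test and 66.6% with a Wald test on the log risk ratio. The latter is closer to the planned summary measure.

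The range is 67-69%, and it is the same for Arm 6 vs 5.

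**Step 3: split the shortfall.**
- Conditional power once the first step has succeeded: 66.9/84.4 = 79%; in the simulation, 81%.
- Loss due to the sequence, against 82%: 82 − 69 = 13 to 82 − 67 = 15 points. In the simulation, where the second test alone has 83.7% power, the loss is 83.7 − 69.4 = 14.3 or 83.7 − 66.6 = 17.1 points.
- Ordinary type II error of the second test: 100 − 82 = 18 points.

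**Step 4: sensitivity to the undefined threshold.** With a first-step threshold of two-sided 10% the joint probability is 73%; with two-sided 20% it is 77%.

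**The case against.** The strongest reply is that the sentence is correct as written. It claims power for each comparison, the arithmetic reproduces, and whenever Arm 4 vs 3 is formally tested its power is close to 80%. The condition is also disclosed, in the text and in Table 2. All of this stands. A reader might infer that the sample size was miscalculated; the figures above show that it was not.

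Three further readings go beyond the documents.
- A reader might say there is a one-in-three chance that the sequence hides a real support effect. About 18 of those 33 points are the type II error that any test with 82% power carries. If the first step fails, the arms are still compared, though only as exploratory.
- A reader might infer a biased support estimate, because success at the first step favours high Arm 3 results. The mean estimated effect given success is 9.4 points against a true 10.0. That is 0.6 points against a standard error of about 3.4, and it arises only when one conditions on that success.
- A reader might conclude that the precondition should go. The plan relies on it as one of its reasons for not adjusting for multiplicity, so removing it is a trade-off and not a correction.

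The reply does not answer one thing. The article lists the two conditional comparisons beside the three unconditional ones under a single power figure, and says nothing about what its own testing rule does to that figure.

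**Conclusion.** The point holds as a matter of what the 80% describes. For Arm 3 vs 1, Arm 5 vs 1 and Arm 2 vs 1 it is the power of the formal test. For Arm 4 vs 3 and Arm 6 vs 5 it is power ignoring the sequence (about 82%) or given success at the first step (about 79-81%). The overall probability of a formal positive result is about 67-69% for each.

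This rests on the plan's assumed rates, household size and correlation all being true, and on a first-step threshold of two-sided 5%. That threshold is the natural reading, but the article does not state it, and a looser one would raise the figure. A regimen effect smaller than 15 points would make the first step fail more often. The issue is one of reporting: arm sizes, estimand, analysis and type I error argument are unaffected.

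**What to change.** In the Sample size section:
- keep 80% power for Arm 3 vs 1, Arm 5 vs 1 and Arm 2 vs 1;
- for Arm 4 vs 3 and Arm 6 vs 5, say that 80% is the power of the comparison on its own, or given that the regimen comparison has succeeded;
- add that the overall probability of a formal positive result is about 67-69% for each under the same assumptions;
- state the significance threshold that counts as showing improved adherence at the first step, and recompute the overall figure if it is not two-sided 5%.

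The cost is a few sentences and a less favourable figure for two comparisons. No extra participants and no change to the testing sequence are needed. The article reports that recruitment had not started, so the wording can be settled before any data exist.

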### Randomisation and allocation

Participants will be randomised centrally using a computerised algorithm developed and maintained by the Medical Research Council Clinical Trials Unit at University College London (MRC-CTU). To randomise a participant, the information contained on a completed Randomisation Form will be entered into the secure online trial database by trial team members at the site who have been trained and authorised to randomise by the MRC-CTU. The database will automatically check for eligibility. Only those who meet all eligibility criteria will be able to be randomised. Randomisation will be performed using minimisation with an additional random element, to be balanced with respect to centre and TB exposure risk group.

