## Introduction

Successful implementation of screening and treatment for latent tuberculosis infection (LTBI) is critical to further reduce TB incidence globally and achieve TB elimination in low TB incidence countries.^1^ A recent call to action issued by the WHO urged for accelerating the scale-up of treatment of LTBI, particularly to mitigate the negative impact from the disruption of TB services caused by the pandemic of COVID-19.^2^

Tuberculosis (TB) in England disproportionately affects underserved communities, such as migrants and homeless people, who consequently experience higher disease burden and worse clinical outcomes. Consequently, in England, LTBI screening and treatment for high risk groups such as new migrants from high TB incidence countries is recognised as an essential strategy to achieve TB elimination.^3^ Contact tracing, including testing and treatment of LTBI among contacts, is another essential component of the TB strategy for England.^3^

Achieving optimal treatment adherence and completion is essential to ensure the efficacy of treatment for LTBI and to achieve commensurate reductions in TB incidence. Standard therapeutic options in the UK include 3 months of self-administered daily isoniazid/rifampicin and 6 months of daily isoniazid; the former regimen is often prescribed because of the availability of fixed-dose formulations and its shorter duration. While these regimen are efficacious in preventing disease, their effectiveness is limited by low treatment adherence and completion rates.^4 5^ According to data from England in migrants whose treatment outcome is known, 75% completed LTBI treatment between 2019 and 2020.^6 7^ The proportion of people who completed treatment varied by Clinical Commission Group (CCG), which was less than 70% in several CCGs.^8^

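### The primary model as stated does not include the two minimisation factors; if they are prognostic, the analysis is slightly conservative and gives up a little power

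*Protocol article*

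**What the plan says.** - **Allocation** (Randomisation and allocation): "Randomisation will be performed using minimisation with an additional random element, to be balanced with respect to centre and TB exposure risk group".
- **Primary model** (Statistical methods): "log-binomial generalised linear mixed models, allowing for intra-household correlation". Household is the only source of dependence named. No covariate is listed, and the text does not describe the analysis as unadjusted.
- **Summary measure** (Statistical methods, Table 2): "Risk ratio for adequate treatment adherence comparing the relevant arms".
- **Sample size**: "A total of 920 participants are to be recruited". "This provides 80% power for each of the following comparisons". The calculation takes no credit for covariate adjustment.
- **Evidence that place matters** (Introduction): "The proportion of people who completed treatment varied by Clinical Commission Group (CCG), which was less than 70% in several CCGs". Completion among migrants with a known outcome was 75% overall. No variance between areas or sites is given.

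The Protocol version and date section says that the article abbreviates protocol V.3.0, which is not shown.

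**The concern.** Balancing arms on a prognostic factor removes that factor's contribution to the real variation of the treatment comparison. A model that leaves the factor out still counts that contribution in its SE. Intervals then come out wider than they need be, and the test rejects less than 5% of the time under the null.

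This is not just a matter of a short article. Statistical methods gives the effect measure, distribution, link, mixed-model structure, analysis population and imputation approach. A statistician following that text would fit arm and household only.

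The stake is modest but real, because some comparisons have little spare power: Arm 2 versus Arm 1 has 80.8%, and Arms 4 versus 3 and 6 versus 5 have 82.0%. The last two are also formally tested only if the corresponding regimen first beats 3HR.

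**Working it through.** **1. Reproduce the plan's own figure.** Inputs from Sample size: 70% versus 85% for the regimen effects and for support with 3HR; 85% versus 95% for support with 3HP and 1HP; two-sided 5%; household size 2; household intra-class correlation (ICC) 0.1. The Abstract gives the 5:5:6:6:6:6 ratio.

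- Arm sizes: 920/34 × 5 = 135.3 and 920/34 × 6 = 162.4.
- Design effect: 1 + (2 − 1) × 0.1 = 1.1.
- Required per arm (pooled variance, no continuity correction): 121 × 1.1 = 133.1 for 70% versus 85%, and 141 × 1.1 = 155.1 for 85% versus 95%.
- Power at 920: 80.8% (2 vs 1), 82.0% (4 vs 3, 6 vs 5) and 84.4% (3 vs 1, 5 vs 1).

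All reach 80% without adjustment, so the stated figures stand.

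**2. Share of variance explained by centre.** The between-centre SD is an assumption. At the average of 70% and 85%, R² = SD² / (0.775 × 0.225) = SD² / 0.1744.

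**3. Effect on the unadjusted analysis of Arm 2 versus Arm 1.** If minimisation balances centre well, the true SE is √(1 − R²) times the model SE.

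- SE excess = 1/√(1 − R²) − 1.
- Actual type I error = 2 × P(Z > 1.96/√(1 − R²)).
- Effective arm size: 135.3/1.1 = 123. Unpooled SE = √[(0.70 × 0.30 + 0.85 × 0.15)/123] = 0.0524. Standardised effect = 0.15/0.0524 = 2.864.
- Power unadjusted = Φ[(2.864 − 1.960)/√(1 − R²)]. Power adjusted = Φ[2.864/√(1 − R²) − 1.960].

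| Assumed SD | R² | SE excess | Type I error | Power unadjusted | Power adjusted | Difference |
|---|---|---|---|---|---|---|
| 0 | 0 | 0 | 5.0% | 0.8169 | 0.8169 | 0 |
| 5 points | 0.014 | 0.7% | 4.8% | 0.8186 | 0.8223 | 0.004 |
| 10 points | 0.057 | 3.0% | 4.4% | 0.8240 | 0.8388 | 0.015 |
| 15 points | 0.129 | 7.2% | 3.6% | 0.8335 | 0.8661 | 0.033 |

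The starting value is 81.7% rather than 80.8% because this step uses the unpooled variance. Unadjusted power does not fall below its starting value: balance shrinks the true SE, and the unadjusted test fails to use all of that gain.

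**4. Simulation check.** Both simulations used 15 centres and 3,000 runs per setting, so the Monte Carlo SE of a 5% rate is √(0.05 × 0.95/3000) = 0.4 points. Small differences between settings should not be read closely.

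- *246 independent participants, two risk groups, biased-coin minimisation.* Unadjusted type I error was 3.7% (factors not prognostic), 4.7% (weak), 4.3% (moderate), 3.6% (strong) and 2.6% (very strong). With strong factors the model SE of the log risk ratio was 0.0890 against a true 0.0834.
- *Households of mean size 2, ICC 0.1, minimisation by household, modified Poisson with household-robust SEs.* Unadjusted type I error was 4.6% (factors not prognostic), 4.9% (centre SD 5 points), 4.1% (10 points) and 3.4% (15 points plus a 10-point risk-group difference).

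**5. Cost of adjusting when the factors are not prognostic.** With main effects, the SD of the log risk ratio was 0.0710 against 0.0700 unadjusted. Full stratification over 30 centre-by-risk cells cost more: power fell from 81.4% to 77.7% with no effect and from 78.3% to 76.1% with moderate effects, and rose only with strong ones (75.8% to 77.3%). The main-effects model with sandwich SEs rejected 5.9% of the time under the null, so it needs a small-sample correction.

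**The case against.** - **Silence is not omission.** The article is abbreviated and gives no covariate list, so the full protocol or a statistical analysis plan may already include both factors. This stands. A reader might infer that the trial's actual analysis leaves them out, but the documents do not show that. The point concerns the model as this article states it.
- **No stated figure is wrong.** This stands too. A reader might infer that the promised 80% power fails or that type I error is inflated. Neither follows: 920 and 80% reproduce without adjustment, and any error is on the conservative side.
- **The size rests on assumptions.** Also true. The Introduction describes routine completion by commissioning area, not pillbox-measured adherence at the 15 expected sites. It makes a centre effect plausible but gives no variance, and nothing shows that risk group is prognostic. At 5 points the loss is close to nil.
- **The 15-point case strains the plan's own ICC.** Households normally sit within one centre. If the ICC of 0.1 includes the centre component, the between-centre SD cannot exceed √(0.1 × 0.1744) = 13.2 points. The 15-point row needs the ICC to be read as correlation within centre, so it is an upper case.
- **Adjustment can lower power.** That result comes from 30-cell stratification. Main-effects adjustment, which is what is proposed here, costs very little.

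**Conclusion.** The point holds in a limited, conditional form. The primary model as stated omits both allocation factors. If they are prognostic, SEs are somewhat too large and the test is slightly conservative. The effect runs from negligible at a 5-point between-centre SD to modest at 15 points (the table above), and it was computed for Arm 2 versus Arm 1 only. It assumes good balance on centre and treats household clustering through the 1.1 design effect. It is a small, avoidable loss of efficiency, not a threat to validity. The reasons to act are that some comparisons have little spare power, and that naming covariates in advance removes a later choice in an open-label trial.

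**What to change.** State in the protocol or the statistical analysis plan that the primary model includes, as main effects:

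- TB exposure risk group as a fixed effect;
- centre as a random effect, or as a fixed effect with a prespecified rule for combining small centres.

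Report the marginal risk ratio, so that the Table 2 summary measure is unchanged. Prespecify a fallback that keeps household clustering if the log-binomial mixed model does not converge, for example a modified-Poisson generalised estimating equation with a small-sample SE correction. Avoid stratifying over every centre-by-risk cell. If the full protocol already does this, one confirming sentence is enough.

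Cost: both variables are already needed for minimisation, so no new data are required. There is slightly more analysis work, some convergence risk, and a very small loss of precision if the factors turn out not to be prognostic. The sample size does not change.
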